## Abstract

**Background:**

Preoperative anxiety and postoperative delirium affect both short- and long-term prognoses in patients with cancer; therefore, these conditions require early prevention and treatment. However, no standard preventive or therapeutic methods have been established for them. Yokukansan, a Japanese herbal medicine for the treatment of insomnia and anxiety, causes relatively few adverse drug reactions and effectively improves the behavioral and psychological symptoms of dementia. Thus, it is expected to be useful for treating and/or preventing perioperative psychiatric symptoms in patients with cancer. The objective of this study is to clarify the therapeutic effect of Yokukansan for preoperative anxiety and its preventive effect on postoperative delirium in cancer patients, as well as to confirm its safety profile.

**Methods:**

This study is a randomized, double-blind, placebo-controlled study in cancer patients scheduled to undergo tumor resection. Patients who provide consent are randomly allocated to receive oral administration of Yokukansan or placebo, and study drug administration is continued for 4 days or longer prior to surgery. We defined two primary endpoints, change in preoperative anxiety and incidence of postoperative delirium. Secondary endpoints are severity score of postoperative delirium, duration of postoperative delirium, amount of benzodiazepines used prior to surgery, amount of antipsychotic agents used after surgery, and number of postoperative hospitalization days. We plan to complete the analysis on March 31, 2021. The target number of registered patients is 110 per group, or 220 in total.

**Discussion:**

This study is the first randomized, double-blind, placebo-controlled study intended to clarify the effects of a Japanese herbal medicine, Yokukansan, in the prevention and treatment of perioperative psychiatric symptoms in patients with cancer. The trial was initiated on August 14, 2017, with 195 subjects randomized by October 5, 2018.

**Trial registration:**

UMIN Clinical Trials Registry (UMIN-CTR), UMIN000027561. Registered on 31 May 2017.

**Electronic supplementary material:**

The online version of this article (10.1186/s13063-019-3202-1) contains supplementary material, which is available to authorized users.

## Background

Patients with cancer experience various psychiatric symptoms during the perioperative period. Anxiety not only lowers treatment compliance by impairing cancer patients’ decision-making ability [1], but it also exacerbates cancer symptoms, leading to reduced quality of life [2]. During the perioperative period, anxiety has also been reported to prolong postoperative pain [3], affect endocrine and immune functions, and influence the progression and long-term prognosis of cancer [4]. An observational study previously conducted at our hospital showed that preoperative anxiety occurred in approximately 15% of cancer patients [5]. Hence, we consider that reducing preoperative anxiety is an important goal of cancer treatment in general.

Delirium is a psychiatric disorder characterized by acute impairment of consciousness and lack of attention [6]. Postoperative delirium refers to delirium that occurs after patients recover from anesthesia, typically within 2 or 3 days after the operation [7–10]. Patients with postoperative delirium experience not only increased rates of respiratory infection and complications associated with immobility and prolongation of hospitalization, but also long-term adverse effects including increased mortality rate [11–13] and impaired cognitive function [14–16]. In the aforementioned observational study, postoperative delirium occurred in approximately 32% of cancer patients [5].

Perioperative psychiatric symptoms should be appropriately assessed, treated, and prevented. However, when used in patients with impaired metabolic capacity, benzodiazepines, which are common therapeutic agents for anxiety, may have long-lasting effects or cause muscle relaxation, resulting in falls. They are also considered to induce delirium when used in patients with cerebral vulnerability, including elderly patients and patients with dementia [17–21]. The antipsychotic agents used for the treatment of postoperative delirium may cause dose-dependent over-sedation or serious adverse drug reactions that include extrapyramidal symptoms and long QT syndrome. Moreover, antipsychotic agents have been reported to increase mortality risk when used in elderly patients with dementia and are often difficult to use in the treatment of elderly patients or patients with heart disease [22–24].

In these contexts, Yokukansan has attracted attention for its potential utility in the treatment of perioperative psychiatric symptoms in patients with cancer. Yokukansan is a Japanese herbal medicine for the treatment of insomnia and anxiety, and it effectively improves the behavioral and psychological symptoms of dementia (BPSD), including hallucinations, delusions, disinhibition, day/night reversal, wandering, irritability, verbal aggression, and risky behavior [25–29]. It has been hypothesized that Yokukansan may prevent postoperative delirium, which presents clinical symptoms very similar to those of BPSD [27, 30–34].

Several lines of empirical evidence imply that Yokukansan would be effective in this context. In a retrospective study (*n* = 19) in patients who underwent colorectal surgery, we found that the incidence of postoperative delirium after Yokukansan administration was lower than in previous studies [35]. In a pre/post study of patients who underwent gastrointestinal surgery (*n* = 8), oral administration of Yokukansan improved insomnia, dysesthesia, restless legs and behavior, and risky behavior [31]. In a randomized phase II trial in which patients underwent cardiovascular surgery (*n* = 30), Yokukansan significantly improved agitation, mood swings, deficient sense of reality, hallucinations, and delusions [33]. In another randomized phase II trial in patients undergoing surgery for gastrointestinal and lung malignancies (*n* = 186) [36], Yokukansan decreased the risk of postoperative delirium in patients with a Mini Mental State Examination score ≤ 26.

Adverse drug reactions, including hypokalemia, have been observed following the use of Yokukansan, but their incidence was no higher than 1.3% (41 of 3141 patients) [37, 38]. On the other hand, benzodiazepines and antipsychotic agents commonly used for these symptoms can cause serious adverse reactions. Although the effect of Yokukansan on anxiety and delirium is less certain than that of benzodiazepines and antipsychotic agents, major adverse events have not been observed following Yokukansan administration, suggesting that this herbal medication may have a major advantage in regard to safety.

Against this background, we planned a randomized controlled study on the efficacy of Yokukansan for perioperative psychiatric symptoms. The objective of this study is to clarify the therapeutic effect of Yokukansan for preoperative anxiety, its preventive effect on postoperative delirium, and its safety in patients with cancer.

## Methods

### Study design

The therapeutic effect of Yokukansan for preoperative anxiety, its preventive effect on postoperative delirium, and its safety in cancer patients will be confirmed in a randomized, double-blind, placebo-controlled study. The investigators registered this study in the UMIN Clinical Trials Registry (UMIN-CTR) https://upload.umin.ac.jp/cgi-open-bin/ctr/ctr_view.cgi?recptno=R000031488 (UMIN000027561) prior to the start of the trial.

### Study setting and sample

We are conducting our study at the National Cancer Center Hospital, a tertiary hospital for cancer in Japan. We are recruiting patients meeting all of the following inclusion criteria: (1) histologically confirmed malignant tumor or clinically confirmed neoplastic lesion that is speculated to be appropriately treatable by resection; (2) scheduled to undergo highly invasive surgery, defined as tumor resection estimated to last 6 h or longer [39]; (3) Hospital Anxiety and Depression Scale-Anxiety (HADS-A) score of at least 1 at the time of registration; (4) ability to take study drugs orally; and (5) age of 20 years or older.

Exclusion criteria are as follows: (1) diagnosis of delirium based on the Diagnostic and Statistical Manual of Mental Disorders, Fifth Edition (DSM-5) at the time of recruitment; (2) use of any Japanese herbal medicine within 4 weeks before the day of registration; (3) history of allergy to Japanese herbal medicine; and (4) hypokalemia rated as grade 2 or higher according to the Common Terminology Criteria for Adverse Events, fourth version (CTCAE v 4.0) within 8 weeks before the day of registration.

The subject accrual period is from August 2017 to March 2019, and we plan to complete the analysis by March 31, 2021.

### Registration and randomization

The investigators are conducting a screening survey of patients scheduled to undergo highly invasive surgery, as specified in the inclusion criteria. The outline of this study is shown in Figs. 1 and 2. The Standard Protocol Items: Recommendations for Interventional Trials (SPIRIT) checklist is provided as Additional file 1.

**Fig. 1 Fig1:**
[figure not shown]
Flowchart of the study procedure

### Intervention

From the day the surgery date was determined to the day before surgery, one packet of the study drug is administered orally three times a day, before or between meals. The intervention group receives Tsumura Yokukansan Extract Granules (TJ-54, Tsumura & Co., Tokyo, Japan). The daily dose of 7.5 g contains the following herbal medicines: Atractylodes Lancea Rhizome 19.5%, Poria Sclerotium 19.5%, Cnidium Rhizome 14.6%, Uncaria Hook 14.6%, Japanese Angelica Root 14.6%, Bupleurum Root 9.7%, and Glycyrrhiza 7.3%. The placebo group receives granules prepared from lactose and other ingredients not containing Yokukansan extract powder, with an appearance and taste formulated to be as similar as possible to those of Yokukansan.

The treatment period is specified as 4 days or longer prior to the surgery. Compliance is rated on the following 3-point scale: (1) at least two-thirds of the dose was taken, (2) at least one-third but less than two-thirds of the dose was taken, and (3) less than one-third of the dose was taken. We prohibit the use of glycyrrhizin and other herbal medicines for 4 weeks before administration of the study drugs.

The HADS-A is used to assess anxiety before and after administration. Subsequently, delirium is assessed daily using the DSM-5 from 1 to 5 days postoperatively. In subjects with delirium only, the severity of delirium is rated using the Delirium Rating Scale-Revised-98 (DRS-R-98), and the duration of delirium is assessed until it resolves or until 30 days after surgery, whichever is later.

### Primary outcomes

#### Change in preoperative anxiety (change in HADS-A score)

Preoperative anxiety is assessed using the HADS-A [40, 41]. The HADS is a self-reported measure of mental status related to depression and anxiety and consists of 14 questions in total: seven pertain to depression (HADS-D), and the remaining seven are about anxiety (HADS-A). Subjects are asked to respond to HADS-A questions on a 4-point scale from 0 to 3; thus, the maximum score is 21. A higher score indicates worse anxiety. In this study, the efficacy of the study drug is assessed by the difference in the HADS-A score before and after oral administration. Researchers ask for the HADS-A results by phone before Yokukansan or placebo is administered for the first time, and they assess the second HADS-A score in the afternoon the day before surgery.

#### Incidence of postoperative delirium

The proportion of patients diagnosed with postoperative delirium is calculated among those in whom planned surgery is completed. In this study, trained psychiatrists or clinical psychologists assess postoperative delirium on a daily basis using DSM-5 [6] within 5 days after surgery. The DSM-5 offers a standard criterion for the classification of mental disorders. Many mental health professionals use the manual to determine a patient’s diagnosis and to communicate this diagnosis to other practitioners.

We clinically demonstrated and discussed our findings on postoperative delirium before this study, with a final determination made once there was satisfactory agreement between the researchers and the principal investigator (SW) regarding the diagnosis of delirium. The researchers assessed patient samples simultaneously and independently to check the inter-rater reliability of the DSM-5 (20 times for each researcher).

### Secondary outcomes

The secondary outcomes are severity score of postoperative delirium assessed by duration of postoperative delirium, amount of benzodiazepines used before surgery, amount of antipsychotic agents used after surgery, and number of days of postoperative hospitalization. The severity of delirium is assessed using the Japanese version of DRS-R-98 [42, 43]. Although this scale rates delirium using the sum of two subscales—the severity score, based on the evaluation of 13 items, and the scores for three items related to diagnosis—this study used only the severity score. Each item is scored from 0 to 2 or 0 to 3, with a higher score indicating a more severe condition.

### Safety outcomes

We define adverse reactions as any undesirable or unintended signs, symptoms, or diseases that occur from the day a study drug is administered through 5 days after surgery. We do not consider events to be adverse reactions if they are judged by the participating surgeons to be related to the surgery.

We describe the details of serious adverse events. The number of cases and the rate are calculated for each study group based on the CTCAE v 4.0. Regarding clinical laboratory values, we calculate summary statistics of changes from actual values and pre-dose values for each treatment group.

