### Statistical analysis

The analysis sets for efficacy and safety include all registered subjects. The mean change in the HADS-A score before and after oral administration in each group, the point estimate of the between-group difference, and the 97.5% confidence interval are calculated. Group means are compared using the *t* test. The incidence of postoperative delirium in each group, the point estimate of the between-group difference, and the 97.5% confidence interval are calculated, and the proportions are compared by the chi-square test. Because there are two primary endpoints, Bonferroni adjustment for multiplicity is performed, and a two-sided significance level of 2.5% is used for the two comparisons. If superiority of the Yokukansan group is observed in either of the endpoints, treatment with Yokukansan will be considered to be useful. The interim analysis examined only the Yokukansan group but not both groups, and we do not regard this as a multiple analysis.

Interim analysis will be performed when the number of subjects who have completed the protocol treatment and are evaluable for both endpoints reaches one-third (*n* = 74) of 220, which is the target number of registered patients in this study. At that time, we will determine whether or not continuation of the study is appropriate. If it is determined that the main purpose of the study has not been fulfilled, the study will be discontinued, and the study results will be promptly disclosed. In principle, registration will not be suspended during the interim analysis. When the point estimate of the mean preoperative anxiety score in the Yokukansan group exceeds 5 points or the incidence of postoperative delirium exceeds 40% in the interim analysis, the Independent Data Monitoring Committee, which consists of three external members, will judge whether or not to discontinue the study.

Serious adverse events are described in detail. For other adverse events, the number of subjects with the highest observed grade and the incidence of the highest grade in each treatment group are calculated, and the groups are compared by the Mantel test.

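### The safety definition drops events that a surgeon judges surgery-related, which may dilute the randomised comparison of postoperative events

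*Protocol article*

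**What the plan says.** Safety is one of three stated aims. The Background section says the trial is to "clarify the therapeutic effect of Yokukansan for preoperative anxiety, its preventive effect on postoperative delirium, and its safety in patients with cancer", and Study design repeats this.

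The Safety outcomes section gives the article's only definition of a safety event. It begins broadly: "We define adverse reactions as any undesirable or unintended signs, symptoms, or diseases". The window opens with the first dose and closes on postoperative day 5. The next sentence narrows the definition: "We do not consider events to be adverse reactions if they are judged by the participating surgeons to be related to the surgery". The same section then covers serious adverse events, CTCAE counts and rates by group, and summaries of laboratory changes by group. None of those sentences repeats the exclusion.

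The between-group safety test is in the Statistical analysis section. It tabulates, by group, the worst grade per subject and compares the groups by the Mantel test: "For other adverse events, the number of subjects with the highest observed grade and the incidence of the highest grade in each treatment group". The term there is adverse *events*. The exclusion is written for adverse *reactions*.

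Two design facts bear on how much the exclusion can remove. Patients must be "scheduled to undergo highly invasive surgery, defined as tumor resection estimated to last 6 h or longer". Study drug is taken "From the day the surgery date was determined to the day before surgery", and "The treatment period is specified as 4 days or longer prior to the surgery".

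**The concern.** The safety window runs past the operation to day 5, and the exclusion acts mainly on that postoperative part. After long, highly invasive surgery, many untoward events can reasonably be put down to the operation, and each one so judged leaves the defined outcome.

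The difficulty is the basis for removal. The rule asks for a causal judgement on a single patient. If preoperative exposure made an ordinary surgical complication more common or more severe, each affected patient would look like a patient with a surgical complication, and the event could properly be called surgery-related. The excess is visible only by comparing arms, and the placebo group is there to measure the surgical background. The rule is also all-or-nothing: an event related to surgery drops out even if the drug contributed.

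At stake is the trial's ability to see a difference in postoperative clinical events. This matters here because the Background section presents safety as a possible major advantage of the drug over benzodiazepines and antipsychotic agents.

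**Working it through.** **1. Does the exclusion reach the between-group test?**

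- For: Safety outcomes is the only place where a countable event is defined, and its wording (any undesirable or unintended sign, symptom or disease) is that of an adverse event under the label of adverse reaction. The Mantel analysis has no other definition to draw on.
- Against: the Statistical analysis section says adverse events, and neither it nor the serious-event sentences mention the exclusion.

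Carry-over is the more natural reading, but it is not certain. The mismatch in terms needs correcting on either reading.

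**2. Which events are exposed?**

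Dosing stops the day before surgery, after 4 days or longer. Events before the operation arise during treatment and can hardly be consequences of the operation, so they should stay counted. Laboratory changes are summarised by group with no attribution step. The exposed events are therefore mainly clinical ones between surgery and day 5.

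**3. What could the exclusion do to sensitivity?**

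The article gives no figure for the safety comparison, no postoperative event rate and no share that surgeons would attribute to surgery. What follows illustrates the mechanism on assumed rates.

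Inputs: n = 110 per group (Sample size calculation). Assumed: a two-sided 5% level, a control risk of 20%, 30% or 40%, and a true risk ratio of 1.5. Presence or absence of an event stands in for the graded Mantel comparison.

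Formula (normal approximation, z = 1.96, d = difference in proportions, p̄ = their mean):

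power = Φ[(d − z·se0) / se1], with se0 = √(p̄(1 − p̄)·2/n) and se1 = √((p1(1 − p1) + p2(1 − p2))/n).

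The corresponding sample-size formula returns the plan's 99 per group for delirium (40% against 20%, two-sided 2.5%, 80% power). The two-means version gives 77 for anxiety against the stated 78. The plan's own figures therefore reproduce, but they say nothing about safety.

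Worked cases at 30% control risk (30% × 1.5 = 45%, a 15-point excess):

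- Nothing removed, 30% v 45%: se0 = 0.0653, se1 = 0.0645, (0.15 − 0.1279)/0.0645 = 0.34, power 63%.
- Half of all events removed in both arms, 15% v 22.5%: se0 = 0.0526, se1 = 0.0524, (0.075 − 0.1032)/0.0524 = −0.54, power 30%.
- Half of the background removed and none of the excess, 15% v 30%: se0 = 0.0563, se1 = 0.0554, (0.15 − 0.1104)/0.0554 = 0.72, power 76%.

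Range when the same share is removed in both arms, whatever the cause of the event:

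| Control risk | 0% removed | 25% | 50% | 75% |
|---|---|---|---|---|
| 20% | 40% | 30% | 20% | 12% |
| 30% | 63% | 46% | 30% | 16% |
| 40% | 85% | 63% | 40% | 20% |

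At 30% control risk, other mixtures give:

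- 80% of background and none of the excess removed (6% v 21%): power 91%.
- 80% of background and half of the excess removed (6% v 13.5%): power 47%.
- 80% of both removed (6% v 9%): power 13%.

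**4. Reading the results.** Loss occurs when surgeons also remove drug-related events in appreciable numbers. A filter that removed background alone would sharpen the comparison. Nothing in the article indicates that a masked surgeon could separate the two in an individual patient.

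**The case against.** The strongest reply is that the exclusion may never touch the comparison. It is written for reactions, the test is described for events, and a plan in which surgeons classify reactions while all events are compared by arm fits the words. The article also condenses a full protocol that is not shown. This stands as a limit on certainty. It does not remove the point, because the exclusion is a stated rule attached to the only definition given, and the article never says that the comparison is exempt.

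Second, a filter that cleared away surgical noise could improve sensitivity. The arithmetic confirms this, provided drug-related events are almost never removed. Individual attribution offers no assurance of that.

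Third, the events most directly informative about the drug occur before surgery and remain counted. This stands. The protocol nevertheless chose to follow safety to day 5, and the rule undercuts that part of its own window.

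A reader might also infer stronger things that the article does not support:

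- *That most postoperative events are discarded.* No section gives a share; many is a reasonable expectation and most is not shown.
- *That excess hypokalaemia, the reaction named in the Background section, would vanish.* Laboratory changes are summarised by group without attribution. If potassium is among the laboratory values, which the article does not list, an excess fall could still appear there.
- *That the rule favours the active arm through biased judgement.* Treatment assignments are masked from study personnel, so no systematic tilt is expected.

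**Conclusion.** The point holds in a limited form. The defined safety outcome is filtered by individual causality judgement in a masked, placebo-controlled trial that names safety as an objective and whose placebo group already measures the surgical background. The consequence is a possible diluted or missed signal for postoperative clinical events. Preoperative events and laboratory summaries are largely unaffected.

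The size cannot be determined from the article. On the assumed 30% control risk and risk ratio 1.5, removing half of all events takes power from 63% to 30%. That rests on drug-related and background events being removed at the same rate, and on the exclusion reaching the Mantel test, which is likely but not settled.

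It would go too far to say that the trial could declare the drug safe because of this counting rule. The article sets no rule for declaring safety from the Mantel test; its only stated success criterion rests on the two efficacy endpoints. The change is worth making because it is cheap and loses nothing now planned.

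**What to change.** 1. Use one term, adverse events, in Safety outcomes and Statistical analysis, and say which events enter each table and test.
2. Make the main safety table, and the input to the Mantel test, all adverse events by arm from first dose to 5 days after surgery, whatever their attribution.
3. Record the surgeon's judgement of relatedness to surgery as a variable for each event, made while masked, and show events judged not surgery-related as a secondary table.

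The cost is more events to code and tabulate, plus a wording change in the protocol and any analysis plan. No extra visits are needed, and the presently defined outcome is still reported, as the secondary table.
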